## Abstract

**Background:**

Intrapartum complications are responsible for approximately half of all maternal deaths, and two million stillbirth and neonatal deaths per year. Prolonged second stage of labour is associated with potentially fatal maternal complications such as haemorrhage and infection and it is a major cause of stillbirth and newborn morbidity and mortality. Currently, the three main options for managing prolonged second stage of labour are forceps, vacuum extractor and caesarean section. All three clinical practices require relatively expensive equipment (e.g., a surgical theatre for caesarean section) and/or highly trained staff which are often not available in low resource settings. The specific aim of the proposed study is to test the safety and feasibility of a new device (Odón device) to effectively deliver the fetus during prolonged second stage of labour. The Odón device is a low-cost technological innovation to facilitate operative vaginal delivery and designed to minimize trauma to the mother and baby. These features combined make it a potentially revolutionary development in obstetrics, particularly for improving intrapartum care and reducing maternal and perinatal morbidity and mortality in low resource settings.

**Methods/design:**

This will be a hospital-based, multicenter prospective phase 1 cohort study with no control group. Delivery with the Odón device will be attempted under normal labour and non-emergency conditions on all the women enrolled in the study. One-hundred and thirty pregnant women will be recruited in tertiary care facilities in Argentina. Safety will be assessed by examining maternal and infant outcomes until discharge. Feasibility will be evaluated by observing successful expulsion of the fetal head after one-time application of the device under standardized conditions (full cervical dilation, anterior presentation, +2 station, normal fetal heart rate).

**Trial registration:**

Australian New Zealand Clinical Trials Registry (ANZCTR). Identifier:
ACTRN12613000141741

## Background

Intrapartum complications are responsible for approximately half of all maternal deaths, and two million stillbirth and neonatal deaths per year
[1-5]. Prolonged second stage of labour is associated with potentially fatal maternal complications such as haemorrhage and infection and it is a major cause of stillbirth and newborn morbidity and mortality. It also increases the risk of vaginal and perineal tears and instrumental deliveries. The three main options for managing prolonged second stage of labour are forceps, vacuum extractor, and caesarean section. The use of forceps and vacuum extractor during prolonged second stage of labour is associated with increased perinatal morbidity
[6-15]. Cephalohematoma and retinal haemorrhages have been associated with the use of vacuum extractor while external ocular injury and facial nerve palsy have been associated with forceps deliveries
[15]. Evidence indicates that vacuum extraction is significantly less likely to achieve successful vaginal delivery than forceps but it is associated with lower caesarean deliveries, probably because forceps are sometimes used after failed vacuum extraction. Vacuum extraction is also contra-indicated in women who are HIV positive or with unknown status. On the other hand, use of vacuum extractor results in lower rates of perineal trauma, tears, requirements for pain relief and incontinence in comparison with forceps
[15].

Caesarean delivery in the second stage of labour accounts for approximately one fourth of all primary caesarean sections
[16]. Although second stage caesarean sections are sometimes appropriate for medically indicated reasons, many of them could be avoided by obstetricians skilled in performing operative vaginal deliveries
[17]. However, fewer health care professionals are receiving appropriate training in operative vaginal deliveries. This change in medical curriculum is contributing to the observed declining trend in the use of operative vaginal deliveries and presents a challenge for maintaining and developing these skills
[18].

### Rationale for the trial: opportunity for development of alternatives

All three available clinical practices for managing prolonged second stage of labour require relatively expensive equipment (e.g., a surgical theatre for caesarean section) and/or highly trained staff that are often not available in low resource settings.

Evidence indicates that the majority of intrapartum deaths in low-resource settings could be prevented through the introduction of innovative strategies that would increase accessibility of obstetric care (e.g., task shifting)
[4]. Technological developments such as the Odón device that reduces the skill level and equipment required to provide quality obstetric care are clearly needed.

The Odón device (see Figure 
1; http://www.odondevice.com/) is envisioned to be a possible alternative to available management options for complicated second stage of labour. It may be potentially safer and easier to apply than forceps/vacuum extractor for assisted deliveries, and a safe alternative to some caesarean sections. It has potential for wide application in low-resource settings, even by mid-level providers. If proven safe and effective, the Odón device will be the first innovation in operative vaginal delivery since the independent development of forceps and the vacuum extractor centuries ago. The Odon device could play a major role in improving intrapartum obstetric care in low resource settings by making possible effective management of intrapartum complications in facilities lacking surgical capacity and/or personnel adequately trained in the use of forceps and the vacuum extractor. Future research may explore additional uses of the device to prevent vertical transmission of infections during childbirth.

**Figure 1 F1:**
[figure not shown]
The Odón device: a new, simple instrument for assisted vaginal deliveries.

### Description of the device and preliminary result in simulators

In comparison with available instruments for operative vaginal delivery (forceps and vacuum extractor), the Odón device presents specific features that could potentially reduce the risk of maternal and fetal injury. The Odón device is made of inexpensive film-like polyethylene material (Figure 
1) and it is designed to be easily applied with the help of an inserter requiring minimal training. The application and use of the Odón device is shown in Figure 
2.

**Figure 2 F2:**
[figure not shown]
Visualization of the use of the Odón device.

Studies in animals have been ruled out for several reasons. In most animals, the head is not the presenting part in normal delivery. Theoretically, experimentation of the Odón device would have been possible in superior primates (chimpanzee, gorilla, and orangutan). However, in practice this option is not feasible because any experimental procedure concerning childbirth with these primates would require general anaesthesia, which would interfere with the physiological mechanisms of labour.

The Odón device was tested under conditions simulating normal delivery at the Simulation Centre of Des Moines University, USA in December 2008. The simulator S 575 (Noelle) which closely simulates a mother-fetus dyad in labour and delivery was used. Under those experimental conditions, the application of the Odón device consistently allowed for the immediate expulsion of the fetus in multiple trials. At that time, the device had never been tested in humans or animal models.

### Study hypothesis and objectives

The main objective of this study is to evaluate the safety and feasibility, in terms of ease of application and successful use of the Odón device in assisting vaginal delivery in singleton term pregnancies during the second stage of labour. The hypothesis is that the Odón device is safe, easy to use, allows for successful delivery, and is accepted by both women and obstetricians.

Safety will be assessed by examining maternal and infant outcomes. Feasibility will be evaluated by observing successful expulsion of the fetal head after one-time application of the device under standardized conditions (full cervical dilation, anterior presentation, +2 station, normal fetal heart rate) in singleton non-complicated pregnancies. Successful expulsion would be defined as the complete expulsion of the head of the baby with the device. Cases of crowning will be recorded. Successful application of the device will be defined as (1) reaching number 4 or 5 in the reading window of the inserter, (2) successful inflation of the device without leaks after the expulsion, and (3) successful expulsion.

### Study conceptual framework

This proposed protocol is embedded in a larger two-phased study:

PHASE 1: the device will be tested for safety and feasibility in terms of ease of application and successful delivery under non-emergency/normal delivery conditions. 130 women will be recruited for delivery using the Odón device. There will not be a control group. This proposed protocol refers to Phase 1 of this study.

PHASE 2: the device will be tested for preliminary efficacy (successful delivery of the baby without the need to resort to caesarean section/forceps/vacuum extractor) in deliveries with prolonged second stage of labour with an indication for not immediate operative delivery (allowing enough time for the application of the Odón device prior to standard of care) and no signs of fetal distress. 128 women will be randomly allocated either to: (1) standard of care (forceps/vacuum extractor); or (2) application of the Odón device. Preliminary efficacy will be assessed by determining the number of successful deliveries by Odón device.

## Methods/design

This will be a hospital-based, multicentre prospective cohort with no control group. Delivery with the Odón device will be attempted under non-emergency/normal delivery conditions on all women enrolled in the study.

### Outcome measures

The different measures collected will be used to assess safety and feasibility. Safety will be assessed by examining maternal and infant outcomes at labour, delivery and immediate postpartum care until discharge. Feasibility will be evaluated by observing successful expulsion of the fetal head after one-time application of the device under standardized conditions as explained above. The list of outcome indicators for Phase 1 are presented in Table 
1.

**Table 1 T1:** Study outcomes

**Labour and delivery**	
**At the time of device application**	• Time from application of device to delivery of the cephalic pole
	• Failure rate of device application (only one attempt will be made)
	• Incidence of:
	○ Operative delivery with forceps or vacuum
	○ Caesarean section
	We anticipate that there may be some cases in which the device will present the following: it cannot be applied, it is difficult to apply, it slips off, or it is ineffective. To determine the clinical circumstances under which such problems occur, the following clinical data will be collected:
	• Position of head
	• Station of head
	• Degree of caput succedaneum and moulding
**During and after delivery**	• Time taken to apply the device (in seconds; from the start to the removal of the inserter)
	• Successful application and inflation
	• Any slipping of the device
	• Number of contractions after application
	• Integrity of the air chamber after expulsion
	• Any other failure of the mechanical failure of the device
**Immediate postpartum period until discharge (24–48 hours)**	
**Maternal**	Incidence of:
	• Episiotomy
	• Lacerations of the low genital tract (vulvar, vaginal or cervical trauma)
	• Perineal lacerations including cervical laceration
	• Third or fourth degree perineal tear
	• Uterine rupture
	• Pelvic hematoma
	• Perineal or vaginal hematoma
	• Postpartum haemorrhage as routinely monitored at the centers
	• Postpartum endometritis or infection
	• Maternal blood transfusion
	• Maternal pain during insertion of the device
	• Maternal satisfaction
**Newborn**	Incidence of:
	• Respiratory rate at 2 hours
	• Birth trauma or injuries (skull fracture, caput succedaneum, cephalohematoma, cutaneous facial lesions and facial palsy, scalp, extracranial haemorrhages, subgaleal haemorrhage, subaponeurotic haemorrhage, intracranial injuries)
	• Low Apgar Scores (less than 7 at 1st minute and less than 7 at 5th minute)
	• Admission to Neonatal Intensive Care Unit
	• Length of stay (> 7 days) in Neonatal Intensive Care Unit
	• Retinal haemorrhage
	• Anaemia
	• Jaundice
	• Evidence of infection by local standards
	• Phototherapy
	• Fetal or neonatal death

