### Data collection, data management and analysis

Case Report Forms (CRF) specifically designed in the WHO Coordinating Unit at UNDP/UNFPA/UNICEF/WHO/World Bank Special Programme of Research, Development and Research Training in Human Reproduction (HRP) for this study will be used for data collection. Data will be collected prospectively by the researchers at the study centres and data checking and entry of the data collection forms will be completed as much as possible at the local centres. Initial data collection will be on paper forms and then data will be entered onto a web-based online open-source data entry system (Open Clinica) developed and coordinated by the trial coordinating unit at HRP. The online data entry system minimizes the delays in data queries and completion of forms. These procedures have been used in previous multicentre trials and proven to be efficient and compliant with the HRP/WHO Standard Operating Procedures and Good Clinical Practice (GCP) guidelines. Similarly, HRP has good experience with online data entry systems from several international multicentre studies conducted in the past five years. Descriptive analysis will be carried out to show the frequencies of maternal and fetal complications, which will be reported as rates or means and 95% confidence intervals.

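### Table 1 puts caput succedaneum in the birth-trauma incidence without limiting it to caput that is new or worse since device application, and puts cervical laceration in the perineal outcome

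*Protocol article*

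**What the plan says.** All outcome definitions at issue are in Table 1 of the protocol article.

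- **Newborn outcomes.** One item in the incidence list begins "Birth trauma or injuries (skull fracture, caput succedaneum, cephalohematoma, cutaneous facial lesions and facial palsy, scalp, extracranial haemorrhages". The bracket then adds two more terms for bleeding and ends with injuries inside the skull. Caput stands in the same bracket as skull fracture and intracranial injury.
- **At the time of device application.** The table also lists "Degree of caput succedaneum and moulding". The stated purpose concerns cases where the device cannot be applied, is hard to apply, slips or does not work: "To determine the clinical circumstances under which such problems occur, the following clinical data will be collected". It is not described as a baseline for the newborn outcome.
- **Maternal outcomes.** One item is "Lacerations of the low genital tract (vulvar, vaginal or cervical trauma" (the bracket closes there). The next is "Perineal lacerations including cervical laceration".

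On design, Methods/design says: "This will be a hospital-based, multicentre prospective cohort with no control group". On analysis, the data section says: "Descriptive analysis will be carried out to show the frequencies of maternal and fetal complications, which will be reported as rates or means and 95%", where the percentage is the level of the interval estimates. It states no composite, threshold or rule for attributing an event to the device.

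**The concern.** Caput has two roles in Table 1, and no text connects them. At application it is a circumstance that may explain trouble with the device. In the newborn it is an injury. A baby whose caput was noted before the device acted, and was no worse at birth, still meets the newborn definition. Women are enrolled at full dilation with the head at station +2 or lower, so part of labour's effect on the head precedes exposure. With no comparison group, that background cannot be subtracted afterwards.

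The second issue is that the bracket mixes caput with the gravest lesions, with no split by severity. Safety is the objective that set the sample size. If the item is published as a single rate, a reader could not tell whether it reflects caput or serious injury, and a change in serious injury would be hard to see.

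The third is a plain error of definition on the maternal side. The cervix is not part of the perineum, yet a cervical tear enters the perineal outcome and also the low genital tract outcome. The perineal rate then does not measure what its name says, and one tear appears under two outcomes.

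**Working it through.** **Step 1: the plan's own figures.** Table 2 gives 95% intervals for n = 130. They reproduce with the exact (Clopper-Pearson) interval, with x = 130p allowed to be non-integer:

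lower = Beta⁻¹(0.025; x, n − x + 1), upper = Beta⁻¹(0.975; x + 1, n − x)

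| Incidence | x | Computed | Table 2 |
|---|---|---|---|
| 2% | 2.6 | 0.35 to 6.14, width 5.79 | 0.4 to 6.1, width 5.8 |
| 10% | 13 | 5.43 to 16.49, width 11.06 | 5.4 to 16.5, width 11.1 |
| 20% | 26 | 13.50 to 27.92, width 14.41 | 13.5 to 27.9, width 14.4 |

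All ten rows agree, so Table 2 contains no numerical error. The same method is used below.

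**Step 2: what one pooled rate would show.** The article gives no frequency for caput or for serious injury. Both are therefore assumptions: serious injury s = 2% (the lowest row of Table 2), caput c from 5% to 50%, the two independent, n = 130.

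pooled = 1 − (1 − c)(1 − s); share of cases with caput only = (pooled − s) / pooled

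For c = 10%: 1 − 0.90 × 0.98 = 0.118, and the share is 0.098 / 0.118 = 83%.

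| Caput (assumed) | Pooled rate | 95% CI | Caput-only share |
|---|---|---|---|
| 5% | 6.9% | 3.2 to 12.7 | 71% |
| 10% | 11.8% | 6.8 to 18.6 | 83% |
| 20% | 21.6% | 14.9 to 29.7 | 91% |
| 30% | 31.4% | 23.5 to 40.1 | 94% |
| 50% | 51.0% | 42.1 to 59.9 | 96% |

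In counts, caput at 10% to 30% is 13 to 39 of 130 babies, against 130 × 0.02 = 2.6 with serious injury. Over caput 5% to 50% and serious injury 1% to 4%, caput-only cases make up 55% to 98% of the pool.

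**Step 3: sensitivity to serious injury.** At caput 20%, tripling serious injury from 2% to 6% moves the pooled rate from 21.6% to 1 − 0.80 × 0.94 = 24.8%. That is inside the 14.9 to 29.7 interval around the first value.

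**Step 4: reported separately.** Serious injury at 2% keeps its own interval of 0.4 to 6.1, as in Table 2, whatever the caput rate. A separate caput rate would still mix pre-existing with new caput unless it is tied to the record at application.

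**Step 5: maternal items side by side.** The low genital tract item names vulvar, vaginal and cervical trauma. The perineal item states that it includes cervical laceration. One cervical tear meets both. No arithmetic is needed.

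**The case against.** The strongest reply is that the article describes no pooled analysis. The bracket can be read as a list of lesions to tabulate one by one, and the analysis section speaks of frequencies in the plural. If each lesion has its own row, nothing is hidden. Component rows may also be set out in a case report form or full protocol that is not shown. This stands: the text fixes neither reading, and Step 2 applies only under pooling. Against it, Table 1 gives some related items their own line (third or fourth degree tears, retinal haemorrhage) but leaves caput, skull fracture and intracranial injury on one.

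A reader might infer that pre-existing caput will be charged to the device and will swamp serious injury. The documents do not support that. They state no attribution rule, no headline trauma rate and no caput rate. The monitoring board is also to review results after every 15 new deliveries in the third recruitment period, so noticing a serious injury need not depend on a pooled percentage.

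Recording caput twice can fairly be called a strength, because it supplies most of what is needed to separate old from new. Caput is also a plausible effect of an instrument on the fetal head, so a first human study has reason to list it. Both points stand, and they argue for linking the two records, not for dropping caput.

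A reader might also infer double counting from the two names, subgaleal and subaponeurotic, for one lesion. Within a single incidence a baby counts once, so this is redundancy. It would matter only if the two were tallied as separate rows.

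**Conclusion.** The point holds in a limited form. As Table 1 is written, caput already present at application qualifies as birth trauma, and the single-arm design offers no background rate to set against it. This holds whether the lesions are pooled or tabulated singly.

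The possible dominance of caput is conditional. It needs one pooled rate, which the article neither states nor excludes, and a caput frequency above that of serious injury, which the article does not give. The range of about 12% to 31% rests on assumed caput of 10% to 30%, serious injury of 2% and independence. It shows what the definition permits and does not forecast a result.

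The perineal wording is a definite error that rests on no assumption. Its harm is a mislabelled perineal rate and one cervical tear listed under two outcomes. No summed maternal total is stated, so no biased total follows.

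**What to change.** 1. Keep caput as a safety item, but take it out of the birth-trauma rate and report it on its own as new or worsened relative to the degree recorded at application.
2. Report serious newborn injuries (for example skull fracture, intracranial injury, subgaleal haemorrhage, facial palsy) separately from minor ones (for example cephalohematoma, skin or scalp lesions), each with its own exact interval. Treat subgaleal and subaponeurotic haemorrhage as one item.
3. Remove cervical laceration from the perineal outcome and make maternal tears exclusive by site: perineal by degree, vulvar or vaginal, and cervical.

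The cost is outcome derivation and reporting, with little or no new data collection. Two details need confirming: that the degree of caput at application is recorded for every woman and not only where the device gives trouble, and that newborn caput is graded in the same way, since a worsening cannot be derived from presence alone.

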### Study population

Pregnant women must meet all of the following inclusion criteria to be eligible for enrolment in the study and application of the Odón device during delivery:

1. Written informed consent obtained during an antenatal care visit, and always before the initiation of labour;

2. Age greater than or equal to 18 years and less than or equal to 35 years;

3. Singleton pregnancy;

4. Gestational age equal to or more than 37 weeks by best estimate according to local protocols;

5. Live fetus by the methods used with local protocols;

6. Fully dilated cervix;

7. Ruptured membranes (spontaneous or artificial);

8. Any anterior occiput presentation;

9. Station level equivalent to 2 cm or more below the spines (e.g. station +2 or lower);

10. Fetal heart rate pattern recorded by continuous fetal electronic monitoring meeting the following criteria:

a. Stable baseline rate between 110 and 160 beats/min

a. normal short and long term variability

a. absence of late decelerations.

### Exclusion criteria

Women presenting any of the following conditions will not be included in the study and the device will not be applied:

1. Suspected or confirmed maternal infection: suspected infection will be diagnosed if any of the following are present:

a) Fever greater than or equal to 38°C

a) Foul smelling amniotic fluid

2. Prolonged rupture of membranes (more than 24 hours)

3. Meconium stained

4. History of coagulation disorder

5. Previous uterine surgery

6. Intrapartum haemorrhage

7. Suspected cephalopelvic disproportion or need of operative delivery

8. Known recto-vaginal Streptoccocus B Haemolyticcus positive culture

9. Known HIV positive status

10. Any condition or circumstance that, in investigator’s opinion, would compromise the safety of the mother or the fetus.

